### Sample size

We based our sample size calculations on limited previous studies capturing the prevalence of depression, suicidal ideation, and suicide attempts [1, 4, 7, 33, 63–71] – as well as distal minority stressors [34, 72, 73] – among SGM persons. For Aim 1, using conservative estimates, we expect a sample size of *N* = 500 in each SGM subgroup to provide a minimum of 98% power (normal approximation with continuity correction) to detect a 15% absolute difference in depression prevalence (estimated prevalence ratio of 1.6) between exposed and unexposed persons. We also expect this sample size to provide at minimum 98% power for a 15% absolute difference in both suicidal ideation and attempts. For the LCA, estimates of minimum required sample sizes in growth mixture models with 10 exposure measures ranged from 300 to 1,100 (in a six-class model with low class separation and 20% missing data) based on Monte Carlo simulations [74]. With an estimated 13 indicators of distal minority stressors, our total sample of 2,500 should therefore be adequate for estimating growth mixture models.

All participants will be followed for 12 months with a projected overall retention rate of 80% resulting in *N* = 400 participants in each SGM subgroup available for endline analyses. We will use the same retention procedures successfully implemented in a recent online prospective pilot study with gay men and other men who have sex with men that demonstrated retention rates of 98% at four months [75]. Though retention is not expected to vary by SGM subgroup, our Aim 2 power calculations account for expected variations in terms of the prevalence and incidence of depression and suicide attempts. Drawing on one general population study of depression incidence over a 24-month period [76], we have used a conservative estimate of average annual incidence of one-eighth of the estimated prevalence. We have also extrapolated from existing cross-sectional studies [7, 34, 66, 72, 73, 77, 78] to estimate that between 25–30% of participants will have additional exposures to distal minority stressors over the follow-up period.

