Due to a lack of available studies, Aim 2 power calculations are based off 24-month rather than 12-month follow-up. We expect the projected sample size in each SGM subgroup followed through 24 months to provide a minimum of 78% power (normal approximation with continuity correction) to detect a 7% absolute difference in depression incidence (equivalent to an estimated incidence rate ratio of 4.5) between exposed and unexposed persons. Notably, these calculations are based on the sexual minority cisgender men subgroup of participants, who are predicted to have the lowest incidence of both depression and distal minority stressors. All other SGM subgroups are expected to have substantially higher power for depression incidence analyses: 84% for transgender men and transmasculine persons; 90% for sexual minority cisgender women; and 99% for transgender women and transfeminine persons.

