For Aim 2, we will use Kaplan–Meier and Cox proportional regression models to describe fixed and time-varying factors/classes and their independent associations with the incidence of self-reported symptoms of moderate or severe depression, suicidal ideation, or suicide attempts during follow-up. Model findings will be reported as adjusted hazards ratios with 95% CIs. Similar to Aim 1 analyses, we will first conduct stratified incidence analyses by SGM subgroups, with subsequent analyses exploring stratification by age and racial/ethnic identities. Guided by our theoretical framework, which combines IPTS with minority stress models, we will also implement mediation models within classes using Structural Equation Mixture Modeling [95, 96]. Secondary analyses will explore recurrent or persistent (as opposed to incident) depression and suicidal ideation using a combination of approaches that can address time-varying, repeated outcomes or changing severity of outcomes [97]. We will also conduct analyses with and without controlling for prior/lifetime reports of major depression, suicidal ideation, and/or suicide attempts, and examine the effects of potential temporality/lag for time-varying exposures that may have overlapped during periods of reported symptoms.

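### The stated minimum 78% power for Aim 2 matches the full 400 retained per subgroup, although participants already depressed at baseline are not at risk of incident depression

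*Protocol article*

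**What the plan says.** The Sample size section takes 500 per subgroup and 80% retention to reach "400 participants in each SGM subgroup available for endline analyses". For Aim 2 it continues: "We expect the projected sample size in each SGM subgroup followed through 24 months to provide a minimum of 78% power". The method is a continuity-corrected normal approximation, and the target is a "7% absolute difference in depression incidence (equivalent to an estimated incidence rate ratio of 4.5") between exposed and unexposed persons. The figure is for sexual minority cisgender men, the subgroup with the lowest expected incidence. The exposed share comes from the estimate that "between 25–30% of participants will have additional exposures to distal minority stressors over the follow-up period". Incidence was derived from prevalence, using a "conservative estimate of average annual incidence of one-eighth of the estimated prevalence".

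The Data analysis section defines the Aim 2 outcome as incidence of moderate or severe depressive symptoms, suicidal ideation or suicide attempts, analysed with Kaplan–Meier and Cox models. It then separates other courses of illness: "Secondary analyses will explore recurrent or persistent (as opposed to incident) depression and suicidal ideation". Table 1 does not exclude people who are depressed at entry, and Aim 1 estimates prevalent depression in the same cohort.

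**The concern.** A participant who already meets the depression definition at baseline cannot contribute a first event. If that person remits and relapses, or stays depressed, the article assigns the course to the secondary analyses. The denominator for the primary incidence question is therefore the retained participants free of depression at baseline, which must be fewer than 400. The article gives no other sample size for Aim 2 and describes no step that removes baseline cases.

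Incidence is one of the two specific aims, and its analyses are run first within each subgroup, so subgroup power is the relevant quantity. If the figure rests on all 400, the stated minimum is too favourable even before the 24-month basis is considered. The article discloses that basis, and it is a separate matter.

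**Working it through.** **Inputs from the Sample size section**
- Retained per subgroup: 500 × 0.80 = 400.
- Risks: a difference of 0.07 with ratio 4.5 gives unexposed 0.07/(4.5 − 1) = 0.02 and exposed 0.09. The ratio is treated as a ratio of risks.
- Exposed share: 25–30%. The exact value for cisgender men is not given.
- Alpha and sidedness: not given. Two-sided 0.05 is assumed.

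**Formula.** With n1 exposed, n2 unexposed and p̄ the pooled risk:
- c = ½(1/n1 + 1/n2)
- SE0 = √[p̄(1 − p̄)(1/n1 + 1/n2)]
- SE1 = √[p1(1 − p1)/n1 + p2(1 − p2)/n2]
- Power = Φ[(0.07 − c − 1.96 × SE0)/SE1]

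**Step 1: reproduce the stated figure with 400**
- 30% exposed (120 and 280): p̄ = 0.041, c = 0.00595, SE0 = 0.02164, SE1 = 0.02743. The bracket is 0.789, so power is 78.5%.
- 27.5% exposed: 77.1%.
- 25% exposed (100 and 300): 75.3%.

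Solving for N, 78% needs about 396 participants at 30% exposed and 428 at 25%. If the 7% and 4.5 are pushed to the limits of their rounding, at least 362 are needed. That leaves room to remove at most 38/400, or about 9.5%.

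**Step 2: how many could be baseline cases?** The article does not state the prevalence for cisgender men. Its own figures give two indications.
- *One-eighth rule, with 2% and 9% read as 24-month risks.* At 30% exposed the mean risk is 0.3 × 9% + 0.7 × 2% = 4.1%. This is 2.05% per year, and × 8 gives 16.4%. At 25% exposed the result is 15.0%.
- *Aim 1 scenario.* A 15-point difference with ratio 1.6 gives 0.15/0.6 = 25% and 40%. The overall level is 28.75% at 25% exposed and 29.5% at 30%, so about 29%.

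**Step 3: power on the at-risk set.** N = 400 × (1 − prevalence), with the same 2% and 9%, test and 24-month basis.

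| Assumed baseline prevalence | At risk | Power, 25% exposed | Power, 30% exposed |
|---|---|---|---|
| None removed | 400 | 75.3% | 78.5% |
| 16.4% | 334 | 67.8% | 70.9% |
| 28.75% | 285 | 60.9% | 63.7% |

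Worked case (285 at risk, 30% exposed, so 85.5 and 199.5): c = 0.00835, SE0 = 0.02563, SE1 = 0.03250. The bracket is 0.351, so power is 63.7%.

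**The case against.** The article never says that all 400 are at risk. That is inferred from the reproduction and from the absence of any other number. Two unstated readings would reconcile 78% with a smaller risk set.

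- *One-sided 0.05.* With 334 at risk and 30% exposed, this gives 78.7%. So 78% does not arise from the full 400 alone. With 285 at risk, however, it gives only 69–73%.
- *Incidence per cohort member.* If 2% and 9% are per cohort member, dividing both by (1 − prevalence) restores power to about 76–79%. The difference among those at risk would then be 0.07/0.836 = 8.4 points at 16.4% prevalence, or 0.07/0.7125 = 9.8 points at 28.75%, and not the 7 points stated.

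The Sample size section also says that its Aim 2 calculations allow for variation in prevalence and incidence. The only use of prevalence it describes is to derive incidence.

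A reader might go further and remove 40% of the exposed and 25% of the unexposed, concluding that the smaller group loses most. The documents do not support that. Aim 1 compares exposure groups cross-sectionally, whereas the 25–30% in Aim 2 are people with additional exposure during follow-up. The 25% and 40% also do not reproduce Aim 1's own 98%: by the same method with 500, they give at most 93.9% (an even split). They indicate an overall level of prevalence, and not a firm one.

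A condensed article may leave the exact risk-set rule to the full protocol. What remains is a published power figure that matches a denominator larger than the stated outcome allows.

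**Conclusion.** The point stands as an overstated power figure whose size depends on assumptions the article leaves out. Under a two-sided 0.05 test, with incidence per person at risk, the stated minimum of 78% corresponds to about 400 participants, the whole retained subgroup. Removing baseline cases lowers it to about 68–71% at 16% prevalence and about 61–64% at 29%. This is a loss of roughly 7 to 17 points from 78%, on the plan's 24-month basis. The loss would disappear if incidence were expressed per cohort member. A one-sided test would remove it only at the lower prevalence.

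A reader might infer similar losses for the other subgroups or for suicidal ideation. Those cannot be quantified. The 84%, 90% and 99% are given without their rates, and no power is stated for incident ideation. Nor should figures for 12 months of follow-up be added to this point, since the article discloses the 24-month basis and that raises a different question.

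**What to change.** Recompute Aim 2 power for each subgroup on the at-risk set, 400 × (1 − assumed baseline prevalence), and replace the stated figures. Beside them, give the assumed prevalence for each subgroup, the exposed share, alpha and sidedness, and say whether 2% and 9% are risks per person at risk or per cohort member. If the original calculation was one-sided or used per-cohort incidence, saying so and giving the at-risk difference would settle the matter.

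The cost is a recalculation and a few sentences. Enrolment, data collection and the planned models do not change. The drawback is that the stated power will probably be less favourable.

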## Methods/design

### Study design

This prospective longitudinal cohort study, “Rural Exploration and Approaches for LGBTQ + Mental Health (REALM),” will explore minority stress in relation to mental health conditions and suicidal behaviors over a 12-month period among rural SGM adults. We will use online processes to recruit and enroll a diverse sample of up to 2,500 SGM adults living in rural counties and small metropolitan areas in the US to complete an online baseline survey. All enrolled participants will subsequently be followed over a 12-month period, with repeated surveys at three-month intervals. The study has been approved by the Johns Hopkins Bloomberg School of Public Health Institutional Review Board (IRB No. 00022255).

This study builds upon prior collaborations between investigators at the Johns Hopkins Bloomberg School of Public Health and the Programs, Research, and Innovation in Sexual Minority (PRISM) Health team at Emory University’s School of Public Health (e.g., [58–62]). Our team of faculty, staff, and students work collaboratively across institutions, drawing upon research, practice, and lived experience in SGM stigma and mental health to inform our work. When constructing our team, we sought inclusion of individuals with diverse sexual orientations and gender identities, alongside interdisciplinary expertise in mental health, SGM health disparities, online survey research, epidemiology, qualitative research, and latent variable modeling.

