### Data collection

Study surveys will be administered online through Alchemer, a HIPAA-compliant survey software platform that stores data in a cloud-based repository which can only be accessed by staff using individual logins and passwords. In addition to a baseline survey, all participants will be asked to complete repeated online surveys administered every three months for a total of 12 months of follow-up post-enrollment (at months 3, 6, 9, and 12). A three-month gap in assessments was chosen to give sufficient time for change to occur in exposure variables without compromising participant recall or retention, or overburdening the participants. Participants will have a total of 60 days to complete each survey from the first date of availability. Participants who miss a survey will be allowed to complete future surveys and will remain in the study unless they request to discontinue participation. Non-fraudulent participants will be compensated $20 in the form of an e-gift card for each completed survey.

Given the risk of mental illness in this population, and survey questions focused on mental health and suicide, procedures have been established to promote the safety of study participants. All participants will be provided with a mental health resource list at the completion of the survey. In addition, survey responses to the Columbia Suicide Severity Rating Scale (C-SSRS) [79] that endorse suicidal ideation with suicide intent or a suicide plan in the last three months will prompt an email alert from the survey software to study clinicians, who are trained in crisis management. Initial outreach will occur within one business day of the email alert to ensure that the participant is safe. Outreach will continue until six contact attempts have been made or the participant is reached, whichever occurs first. Study clinicians will also reach out, up to three times, to emergency contacts if other methods are unsuccessful. Once contacted, study clinicians will assess the participant’s level of risk and conduct safety planning, lethal means counseling, and/or connect the participant to a crisis hotline, as deemed appropriate by the clinical staff member.

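### Aim 2 power is given only for 24 months of follow-up, but the study follows participants for 12; taken as written, the 78% minimum becomes about 46–49%

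*Protocol article*

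**What the plan says.** Follow-up is 12 months throughout the protocol article. Study design describes follow-up "over a 12-month period, with repeated surveys at three-month intervals". Data collection specifies "12 months of follow-up post-enrollment (at months 3, 6, 9, and 12", with no later survey. Sample size says "All participants will be followed for 12 months with a projected overall retention rate of 80" per cent, leaving "400 participants in each SGM subgroup available for endline analyses".

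The next paragraph of Sample size changes the horizon: "Due to a lack of available studies, Aim 2 power calculations are based off 24-month rather than 12-month follow-up". It expects each subgroup "followed through 24 months to provide a minimum of 78% power" for a 7-point absolute difference in depression incidence, described as a rate ratio of 4.5. That minimum is for sexual minority cisgender men. Figures of 84%, 90% and 99% follow for three other subgroups, and none is given for non-binary persons. No 12-month power appears. The same section says the incidence input was an average annual incidence equal to one-eighth of prevalence, and that 25–30% of participants would be newly exposed during follow-up.

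**The concern.** Aim 2, on incidence, is one of only two specific aims, and its only stated power belongs to a study twice as long. Under a roughly constant rate, halving the follow-up roughly halves the number of events, and with an uncommon outcome power depends mainly on the event count. The sample size is mismatched too: 400 is the number expected to remain after 12 months, and no allowance is made for loss over a second year.

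The reason given, a lack of suitable studies, does not rule out a 12-month calculation, because the plan already works from an annual incidence. At stake is how Aim 2 subgroup results will be read. A null result in cisgender men from about eight events would be set against a stated power of 78%, and readers are told neither the size nor the direction of the discrepancy.

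**Working it through.** **Inputs from Sample size.** N = 400 per subgroup (500 × 0.80); difference 0.07; ratio 4.5; 25–30% exposed; normal approximation with continuity correction. The significance level is not stated, so two-sided 5% is assumed.

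**1. Implied risks.** Unexposed: p0 = 0.07/(4.5 − 1) = 0.02. Exposed: p1 = 0.02 + 0.07 = 0.09.

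**2. Reproduce the plan's figure.** With n1 exposed, n0 unexposed and p̄ the pooled risk:

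- SE0 = √[p̄(1 − p̄)(1/n1 + 1/n0)]
- SE1 = √[p1(1 − p1)/n1 + p0(1 − p0)/n0]
- c = 0.5(1/n1 + 1/n0)
- power = Φ[(p1 − p0 − c − 1.96·SE0)/SE1]

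At 30% exposed (n1 = 120, n0 = 280): p̄ = 0.041, SE0 = 0.02164, SE1 = 0.02743, c = 0.00595. Power = Φ[(0.07 − 0.00595 − 0.04240)/0.02743] = Φ(0.789) = 78.5%. At 27.5% exposed it is 77.1%, and at 25% it is 75.3%. The stated 78% is reproduced toward the upper end of the exposure range.

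**3. Same method at 12 months, reading 2% and 9% as 24-month risks.** Under a constant rate, p12 = 1 − √(1 − p24). This gives 1 − √0.98 = 1.005% and 1 − √0.91 = 4.606%, a difference of 3.6 points. Simple halving gives 1.0% and 4.5%.

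| Exposed | 24 months | 12 months, halved | 12 months, constant rate | Expected events at 12 months |
|---|---|---|---|---|
| 25% | 75.3% | 45.6% | 47.1% | 7.5–7.6 |
| 30% | 78.5% | 47.5% | 49.0% | 8.2–8.3 |

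**4. Sensitivity to method (12 months).** With the constant-rate risks, Fisher's exact test gives 54–56%, and the normal approximation without continuity correction gives 59–61%. The planned analysis is Cox regression, so a Schoenfeld check is relevant: power = Φ[√(D·e(1 − e))·ln 4.5 − 1.96], with D events and exposed share e. At e = 0.30, 16.4 events give 79.7% and 8.2 events give 50.5%. At e = 0.25, 15 events give 71.3% and 7.5 give 43.0%. No method restores 78%.

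**5. What 12 months can detect.** With N = 400 and a 12-month unexposed risk of about 1%, 80% power needs an exposed risk of about 7.2% (30% exposed) to 7.6% (25% exposed), a ratio of about 7.2–7.6. Keeping a ratio of 4.5 and 78% power needs about 810–877 analysed per subgroup (halved risks).

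**6. Are 2% and 9% really 24-month risks?** Averaged over 25–30% exposed they give 0.25 × 9 + 0.75 × 2 = 3.75% to 0.30 × 9 + 0.70 × 2 = 4.1%. For Aim 1, a 15-point difference with a ratio of 1.6 implies 0.15/0.6 = 25% against 40%. With the same exposed shares (an assumption), average prevalence is 28.75–29.5%. One-eighth of that is 3.6–3.7% a year, or about 7.2–7.4% over two years. The 3.75–4.1% therefore fits an annual risk much better. Read as 24-month risks, the annual average is 1.875–2.05%, which implies a prevalence of only 15–16.4%.

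**7. If they are annual risks.** The 75–78.5% in step 2 is already the 12-month power. The 24-month risks would be 1 − 0.98² = 3.96% and 1 − 0.91² = 17.19%, with power of about 96–97%.

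**The case against.** The strongest reply is that the 24-month basis is disclosed, with a reason, in the same paragraph as the figures, and that the 78% is correctly computed for what it claims to be. That stands as far as it goes: nothing is concealed and the formula was not misapplied. But saying that a calculation describes a longer study does not supply one for this study.

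A reader might infer that the true power in cisgender men is simply about 47–49%. The document does not support so firm a statement. Step 6 gives a real reason to think the risks are annual, in which case the label is at fault and no power is lost. This is not conclusive either: the text twice says 24 months, and Aim 1's implied prevalence is not stated to be that of cisgender men. The reproduction also has some slack. The significance level is assumed, and cisgender men are said to have the lowest exposure, which points to the 25% end, where the method gives 75.3%.

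A reader might also scale down the 84%, 90% and 99% by halving the information. Those subgroups' incidence and exposure inputs are not given, so their 12-month values cannot be computed. Only the direction follows: on the text as written, they too are overstated.

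**Conclusion.** The point stands in conditional form. The only Aim 2 power in the protocol article is for 24 months, and the study ends at 12. If 2% and 9% are cumulative 24-month risks, as the wording says, minimum power at the actual follow-up is about 46–49% by the plan's own method and about 54–61% by Fisher's exact test or without the correction. This assumes two-sided 5%, N = 400, 25–30% exposed, and a ratio of 4.5 that holds at 12 months. Removing people already depressed at baseline from the 400 would lower it further; with N = 340 it is about 40–41% (halved risks). If the risks are annual, 78% is the 12-month figure and the 24-month description is wrong. The document alone cannot settle which reading applies, but under both the paragraph misdescribes the study's power.

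**What to change.** In the Sample size section:

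- State whether the incidence inputs behind the 7-point difference are annual or 24-month risks.
- Replace the 24-month figures with power at the actual 12-month follow-up, or keep them labelled as not applicable to this design beside the 12-month values.
- Give the 12-month power for all five subgroups, including non-binary persons, with each subgroup's incidence, exposed share and significance level.
- State the smallest rate ratio detectable with 80% power at 12 months.

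If the inputs are 24-month risks, convert them with 1 − √(1 − p24) under a constant rate. The cost is a short recalculation and some rewording, with no change to enrolment or follow-up. The only downside is that the stated power may look less favourable.

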### Recruitment

Study participants will primarily be recruited through geo-targeted advertisements on social networking websites and mobile applications, including Facebook, Instagram, Snapchat, YouTube, Tumblr, Reddit, X (formerly Twitter), TikTok, Tinder, and Grindr. In addition, a list of rural SGM-serving organizations will be compiled and asked to promote the study both by sharing advertisements on their websites, social media pages, and email lists as well as by distributing recruitment materials during in-person SGM-focused events. Recruitment will also be conducted via referral from other participants, the CAB, and the study team. Individuals who click on ads will be referred to a brief introduction script and will complete a self-administered eligibility screening survey through a secure online platform. If they are found to be eligible based on the screener, potential participants will be emailed a unique link to complete informed consent and the baseline survey. Study materials – including the recruitment materials, screening survey, and questionnaires – will be available in both English and Spanish to allow for the recruitment of rural Spanish-speaking SGM populations.

Participants will be enrolled in the study only upon validation (e.g., ensuring that participants are non-fraudulent and are not survey bots). The validation process will occur after the completion of the baseline survey and will be comprised of both manual and automated procedures. These will include phone number verification, IP address location verification, zip code confirmation, time-stamp review, duplicate enrollment check, review of survey responses for mismatched answers on repeat questions, completion of the baseline survey within 28 days of receipt, and completion of at least 75% of the baseline survey and mental health questions. Participants who do not pass this validation process will be marked as ineligible and stopped from participating in further study activities.

